### 3.3 Study design

This study is a pilot single-site randomized sham-controlled interventional clinical trial based at the Interventional Psychiatry Program, St. Michael’s Hospital – Unity Health Toronto (UHT) in Toronto, ON, Canada. The trial will compare a course of 10 sessions of 130 Hz tTIS stimulation vs. 10 sessions of sham stimulation, delivered over 2 weeks (Figure 1). Thirty participants with MDD will be recruited into the trial and randomized into two parallel arms (active tTIS vs. sham) in a 1:1 fashion. Block randomization will be stratified by sex to allocate participants using a secure randomization module on Research Electronic Data Capture (REDCap) (Harris et al., 2009), as sex differences in brain volume and skull anatomy influence NIBS treatment outcomes (Hanlon and McCalley, 2022). Participants, investigators, outcome assessors, and data analysis will be blinded to treatment allocation. A randomization table will be generated using an external tool and uploaded to REDCap. Once a new participant is ready to be randomized, a research coordinator external to the study will enter their sex (a stratification variable) into REDCap, and the system will use the pre-defined randomization table to assign them to a treatment group.

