### 3.4 Sample size considerations

Based on studies in TES with fMRI, block design, and use of computational iterative neurostimulation (Ghobadi-Azbari et al., 2021), we expect that 30 participants will have adequate power to demonstrate target engagement of the sgACC. The proposed sample size (*n* = 30) is also based on the overall goal of (a) reasonably assessing the feasibility outcomes and (b) estimating the variability of the clinical outcome measures and is consistent with published recommendations for pilot trials designed to estimate standard deviations for larger future randomized controlled trials when the effect size is small-to-medium (Lancaster et al., 2004; Whitehead et al., 2016). As such, based on sample sizes used in pivotal TES studies (Berlim et al., 2013), we expect that 30 participants will be adequate to demonstrate the feasibility, tolerability, safety, and therapeutic effect of tTIS. Moreover, the pilot study will provide effect size estimates to design a definitive efficacy trial.

For this pilot study, to have a 90% power (i.e., being 90% confident that the effect is true and that it is not a type I/II error), the top end of the two-sided 95% confidence intervals will be the maximum confidence of having a true difference between active tTIS and sham arms. If there is no difference between active tTIS and sham arms, then *p* ≥ 0.051 will indicate no difference with a 90% confidence, and if there is a difference, then *p* ≤ 0.05 will indicate the difference with a 90% confidence. To have the medium effect size of *f* = 0.25 for the mixed-model analysis of variance (Cohen, 2013), 30 patients (15 per group) are required to have a 90% power. We anticipate having a 15% dropout rate in the randomized phase of the study due to side effects or lack of adherence to protocol and approximately a 50% response rate in the acute phase of treatment. A sample size of 15 per group will give us precise estimates of variability in the clinical outcome, namely a change in the Hamilton Depression Rating Scale 17-Item (HAM-D-17) (Hamilton, 1960) score over time (Korn et al., 2012; Cohen, 2013), and this sample size is within the recommended total sample sizes for a precise estimate of the standard deviation and correlation for HAM-D-17 scores to use in the future sample size calculation for a definitive larger scale trial (between *n* = 24 and 50) (Julious, 2005; Sim and Lewis, 2012; Billingham et al., 2013).

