#### 3.12.2 Secondary outcomes: clinical assessments

Improvement in depressive symptoms will be the main secondary outcome measure. Additional secondary outcome measures will include feasibility, safety, and tolerability metrics of rates of recruitment, withdrawals, and adherence, as well as the number and nature of AEs and serious AEs.

For continuous outcome measures, a mixed-effects model will be used to assess differences in the rate of improvement over time and the final outcome across groups. Treatment group, time, and treatment group × time interaction will be used as explanatory variables, with participant as a random factor. The significance of the treatment group × time interaction effect will be used to test the null hypothesis. For categorical outcome measures, response will be defined as a ≥50% reduction in HAM-D-17 and QIDS-SR-16 total scores at Visit 10. Remission will be defined as a HAM-D-17 total score of <8 at Visit 10. The two-tailed Chi-squared test will be used to assess the significance of any observed differences in the proportion of responders and remitters between groups.

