#### 3.12.3 Secondary outcomes: electroencephalography

EEG data will be acquired at Visits 1, 5, and 10 to provide a time-series representation of changes in neural activity over time and after a single session of tTIS. These analyses will be exploratory. Two sets of recordings, before and after the tTIS or sham stimulation, will allow us to examine the immediate effect of the stimulation. Recording EEG signals during the stimulation will offer insights into the feasibility of conducting concurrent tTIS-EEG recordings, as well as source signal propagation.

EEG signal analysis will be done using MATLAB, and the preprocessing steps will include signal noise and artifact removal. Independent component analysis (ICA) will be used to remove electrooculogram (EOG) artifacts. EEG signals will be bandpass filtered at 0.5–40 Hz to remove movement and instrumentation noise. A simple power estimation will be conducted on the resting-state EEG signals. Time and frequency domain analysis will be conducted on segmented auditory MMN EEG signals. The segmentation will divide the EEG signals into short-term epochs of 500 ms (−100 to 400 ms). The analysis will then be conducted on these time segments. Time domain analysis will be used for the auditory MMN tasks to estimate the average difference between deviant and standard ERP responses in order to extract the amplitude and latency of N1 and P1 ERPs. Time domain signal processing techniques will be used to extract statistical metrics such as root mean square, signal variance, and variance of the first derivative of the ERP signals. Frequency domain analysis on the segmented EEG signals will extract energy ratios and power spectral density at each EEG frequency band. Subjective answers obtained as categorical variables will be used in labeling the EEG segments, and machine learning techniques will be implemented to classify the signal segments on the basis of response and remission as well as to determine the combined role of MRI metrics, clinical variables, and EEG signal features in assessing treatment response to tTIS.

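### Section 3.12.3 classifies EEG segments by response and remission, which exist once per participant, so accuracy is inflated if one person's segments reach both training and test data

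*Protocol article*

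**What the plan says.** Section 3.12.3 (EEG) describes the segmentation of the mismatch-negativity recordings: "The segmentation will divide the EEG signals into short-term epochs of 500 ms", and the analysis is then run on those segments. On labels it says "Subjective answers obtained as categorical variables will be used in labeling the EEG segments", and on prediction that "machine learning techniques will be implemented to classify the signal segments on the basis of response and remission". The same sentence adds an assessment of how MRI metrics, clinical variables and EEG features together relate to treatment response, without naming a unit. The section calls the EEG analyses exploratory.

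Section 3.12.2 defines the two outcomes: "response will be defined as a ≥50% reduction in HAM-D-17 and QIDS-SR-16 total scores at Visit 10", and "Remission will be defined as a HAM-D-17 total score of <8 at Visit 10".

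On numbers, section 3.3 says "Thirty participants with MDD will be recruited into the trial and randomized into two parallel arms", and section 3.4 says "We anticipate having a 15% dropout rate in the randomized phase of the study".

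**The concern.** The case that is labelled and classified is the segment, but the label belongs to the person. A half-second epoch cannot respond or remit. It inherits one value from its owner, as do all of that person's other epochs.

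This matters in two ways. First, segments of one person resemble each other to some degree. If some are used for training and others for testing, a classifier can score well by matching a test segment to the same person's training segments, without learning anything about response. Second, the precision of any accuracy depends on the number of people, not the number of segments. An accuracy stated over thousands of segments would look far more certain than about 26 to 30 labels allow.

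At stake is whether the reported ability of EEG features to predict response to the stimulation can be interpreted.

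**Working it through.** The plan gives no accuracy, sample size or power for this analysis, so there is no figure of its own to reproduce.

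**Independent labels.** 30 participants are randomised (section 3.3). With 15% dropout (section 3.4), 30 × 0.85 = 25.5, about 26, would have a Visit 10 outcome.

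**Segments.** Section 3.11 gives a 3-minute mismatch-negativity block before and after stimulation at Visits 1, 5 and 10. The stimulus interval is not given. If epochs are contiguous (an assumption):

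- per block: 180 s / 0.5 s = 360
- per participant: 360 × 2 blocks × 3 visits = 2,160
- in total: 2,160 × 30 = 64,800, or 2,160 × 26 = 56,160

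That is up to tens of thousands of cases for 26 to 30 labels.

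**Null simulation.** Feature k of segment j in participant i is √ρ·u(i,k) + √(1−ρ)·e(i,j,k), with u and e independent standard normal and ρ the within-person correlation. Labels are half responders, in line with the roughly 50% response rate anticipated in section 3.4, and are assigned independently of all features, so true accuracy is 50%. The documents do not give ρ, the number of usable segments, the features or the classifier. All of these are assumptions.

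26 participants, 60 segments each, 12 features:

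| ρ | Nearest neighbour, segments split at random | Linear discriminant, segments split at random | Whole participants held out |
|---|---|---|---|
| 0.2 | 59% | 61% | about 50% |
| 0.5 | 84% | 68% | about 50% |
| 0.7 | 97% | 73% | about 50% |

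A repeat run agreed to within about one percentage point.

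30 participants, 100 segments each, 20 features, 5-fold cross-validation:

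| ρ | Nearest neighbour, folds by segment | Linear discriminant, folds by segment |
|---|---|---|
| 0 | 50% | 50% |
| 0.1 | 54% | 59% |
| 0.3 | 75% | 66% |
| 0.5 | 95% | 72% |
| 0.8 | 100% | 83% |

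With folds by participant, this second setting gives 49% to 51% (nearest neighbour) and 48% to 52% (linear discriminant) over the whole range of ρ.

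**Error bars with participants held out.** Take 26 participants with 100 segments each, so 2,600 segments. The standard error of a 50% accuracy that counts segments is √(0.25/2,600) = 0.0098. The spread of accuracy actually seen over 20 simulated trials, with folds by participant, was:

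- ρ = 0.1: 0.019 (nearest neighbour) and 0.044 (linear discriminant), ratios 1.9 and 4.5
- ρ = 0.3: 0.033 and 0.060, ratios 3.4 and 6.1
- ρ = 0.5: 0.050 and 0.079, ratios 5.1 and 8.1
- ρ = 0.8: 0.062 and 0.075, ratios 6.3 and 7.7

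So for ρ of 0.1 or more, segment-based error bars are about 2 to 8 times too small even when the split is right. With 20 replicates these ratios are approximate.

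**The case against.** The strongest reply is that the split, not the unit, causes the inflation. The simulations show this: the same segments and labels give about 50% once whole participants are held out. The article names no split, and a condensed article may leave cross-validation to a fuller document. Its silence there is no error, and the stated text is compatible with a valid analysis. This largely stands. It does not dispose of the point, because the article does fix the unit of classification, and that unit gives misleading precision even under a correct split.

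Other parts of the reply also stand:

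- A reader might infer that the plan treats segments as independent cases, or that its classifier will merely recognise people. The article says neither. Both depend on a split that it does not describe.
- A reader might infer that segments of one person are near-identical. Nothing in the article says so. Moderate correlation is enough for inflation, and at zero correlation there is none.
- Nearest neighbour is especially prone to this leakage, so its figures alone would overstate the size. Linear discriminant analysis is inflated less at moderate and high correlation.
- A reader might extend the fault to the combined MRI, clinical and EEG analysis. That clause names no unit, so the text does not support it.
- The labelling clause about subjective answers is unclear, and some labels might vary by visit. Response and remission, however, are tied to Visit 10.
- A reader might infer that a spurious accuracy will be carried into the definitive trial. The abstract says that the trial's data will inform its design, but section 3.4 refers to effect sizes and the variability of HAM-D-17, and nowhere is classifier accuracy named as an input.

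**Conclusion.** The point holds in a limited form. Sections 3.12.2 and 3.12.3 together set a unit of classification (the segment) that does not match the label (the participant), and only about 26 to 30 labels are independent.

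If one person's segments are shared between training and test data, accuracy with no signal rises to roughly 60% at a within-person correlation of 0.2 and to 73% to 97% at 0.7, depending on the classifier. Holding out whole participants removes this bias, but does not make it valid to count segments when stating precision. The sizes rest on assumed correlations, features and classifiers. The mismatch itself rests only on the text.

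The consequence is confined to the exploratory EEG prediction result. The imaging primary outcomes, the main secondary outcome of depressive symptoms and the sample size are untouched.

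**What to change.** In section 3.12.3, state that response and remission are classified at participant level, in one of two ways:

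- average the segment features within each participant before classification, or
- keep segments, but place all segments and visits of a participant in the same fold, for example by leaving one participant out at a time, with feature selection and tuning done inside the training folds.

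In either case, report participant-level accuracy or AUC, and test it by permuting labels across participants rather than across segments.

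The cost is a change of wording and analysis code, with no new data and no effect on trial conduct. The downside is that the reported accuracy will be lower and less precise, which is what 26 to 30 labels can support.

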### 3.13 Early withdrawal and study termination

Participants are free to withdraw from the study at any time without penalty or loss of benefits. A participant will be discontinued if they miss more than three treatment sessions, are non-compliant, experience worsening depression, meet exclusion criteria at a later time point, experience severe side effects, or if the stimulation device is believed to be unsafe. This study may be terminated if there is sufficient reasonable cause.

## 4 Discussion

The therapeutic effectiveness of NIBS in MDD has been validated across numerous studies, but, with few exceptions (Cole et al., 2020, 2022), its efficacy remains limited due to its dependence on the selection and accuracy of stimulation targets (McLoughlin et al., 2007; Herbsman et al., 2009; Fox et al., 2012; Berlim et al., 2013; Lefaucheur et al., 2017; Liu et al., 2017). Guiding NIBS with cutting-edge imaging techniques is fundamental for locating specific functional brain networks and accurately positioning stimulation sites to fit individual anatomical variations (Mir-Moghtadaei et al., 2015; Luber et al., 2017). To develop NIBS as an individualized treatment for individuals with MDD, determining a combination of suitable imaging methods is crucial for providing optimal antidepressant effects. Our clinical trial is a multi-modal neuroimaging study, where target engagement of the sgACC will be assessed across different modalities and metrics, spanning both structure and function. These data will guide the investigation of the target engagement capabilities of tTIS as a new, emerging technology that can potentially be enabled for personalized and precision psychiatry in the future.

The preliminary studies establishing its safety and effectiveness in healthy humans, as well as its unique spatial accuracy, make tTIS a desirable candidate for NIBS therapy in MDD (Wessel et al., 2021; Ma et al., 2022; Piao et al., 2022; von Conta et al., 2022; Zhang et al., 2022; Zhu et al., 2022). The present study will be the first to demonstrate target engagement of the sgACC and the therapeutic potential of repetitive tTIS in MDD. Data from this trial will provide much-needed safety and effectiveness evidence to the limited literature regarding tTIS for deep brain regions in humans. If successful, our approach of noninvasively targeting sgACC may also be translated to other psychiatric disorders of disrupted brain connectivity characterized by sgACC dysregulation and FC disturbances.

It should be acknowledged, however, that our electrode configuration is based solely on finite element simulations as the configuration that led to the highest tTIS “beat” field strength in the sgACC in three head models. This configuration, ideally, should be validated for target engagement in a single-session experiment among healthy participants using task-based functional neuroimaging. Additionally, off-target high-field strengths are impossible to avoid, given the location of the target and the geometry of the brain. Therefore, the effects of this configuration should also be validated against other brain areas in close proximity to the sgACC, such as the dorsal anterior cingulate cortex. Furthermore, as demonstrated by previous studies that applied tTIS in humans (Violante et al., 2023; Wessel et al., 2023; Vassiliadis et al., 2024a), treatment effects of tTIS can be enhanced if the stimulation is applied during a behavioral task engaging the target region. However, selecting an optimal behavioral task to engage the sgACC remains a challenge, as the seminal literature showing sgACC hyperactivity in depression (George et al., 1995; Mayberg et al., 1999) used transient sadness induction or autobiographical memory tasks, which are highly subjective, difficult to standardize across participants, and lacking quantifiable accuracy responses. Since then, no task has been validated specifically for the engagement of the sgACC, and future work should focus on addressing this shortcoming. In our trial, therefore, changes in absolute BOLD signal may not be as pronounced during the resting-state scan acquisition, although resting-state scans may be more optimal for examining the FC of the sgACC with multiple intrinsic brain networks simultaneously, as well as the association between brain network dynamics and anatomical connectivity (Lv et al., 2018; Al-Arfaj et al., 2023).

The chance to develop new treatments for MDD is an important step in helping people who suffer from this condition. This study may offer individuals with MDD a novel treatment option, which can be beneficial for those who are resistant to antidepressants and psychotherapy or who cannot tolerate other forms of NIBS. Moreover, tTIS is relatively easy to administer: device electronics are simple, and devices can be made smaller for home use. The devices are also low-risk, and patients can be educated on how to self-deliver the stimulation. Unlike its sister technology, TMS, tTIS is a form of tACS that has the potential to be scalable. At-home devices are already emerging, which potentially makes tTIS a cheaper and safer technology. This is advantageous, both in terms of the economics of healthcare provision and the logistics of future large-scale clinical trials. Our study is thus a first step for readapting tTIS for home-based delivery, which will benefit individuals with high functional impairment and limited access to in-hospital treatment programs.

Although participants may experience some degree of relief from mood symptoms due to a course of tTIS, this study has not been designed to benefit the individual participant. Side effects from tTIS/tACS reported in the literature are limited but are not nonexistent; the most common include mild tingling, itching, burning, discomfort or pain, visual sensation, moderate fatigue, skin redness, headache, and difficulties in concentration (Antal et al., 2008; Feurra et al., 2011; Brignani et al., 2013). Due to scheduling restrictions, treatment sessions will only be completed on weekdays, resulting in a 2-day gap between certain sessions. No evidence to date reports this as a limitation, but it is possible that this delay between treatment sessions may affect the treatment outcomes. Furthermore, the stimulation parameters for our tTIS paradigm have been chosen while keeping in mind the goal of minimizing dropout rates in our clinical trial, as tTIS will be administered in a repetitive fashion over 10 days.

The human tTIS studies published to date (Violante et al., 2023; Wessel et al., 2023; Vassiliadis et al., 2024a) are single-session studies in which tTIS was delivered to healthy participants. These studies applied the stimulation at frequencies close to 2 kHz. In our proposed study, tTIS will be delivered at frequencies close to 1 kHz, as it may offer advantages in terms of safety, efficiency, and patient comfort associated with repetitive administration of tTIS – higher frequencies may be associated with more pronounced side effects such as discomfort, phosphenes, and involuntary muscle contractions (Liu et al., 2024). Tissue heating and electrical impedance in biological tissue also increase with frequency (Liu et al., 2024), and using 1 kHz may minimize these risks. In addition, some of the abovementioned studies included tACS as an active high-frequency control instead of the 0-mA sham proposed in this study (Wessel et al., 2023; Vassiliadis et al., 2024a). Absolute stimulation frequencies in the tACS active control arm were equivalent between the two channels and did not generate the neuromodulatory “beat” frequency. This design offers advantages for a basic science experiment aiming to ensure that the target engagement effects are specific to the tTIS “beat” frequency in a desired locus and not due to general electrical stimulation. In our clinical trial, however, the goal is also to ensure any observed change in depressive symptoms is due to the verum tTIS and not other factors such as placebo effects, therapeutic response to high-frequency stimulation, or engagement of off-target superficial cortices with active tACS. Active tACS as a control is likely to lead to a meaningful change in depressive symptoms if areas of the dlPFC are engaged (Alexander et al., 2019; Wilkening et al., 2019; Haller et al., 2020; Riddle et al., 2022), which may mask the true therapeutic effect of active tTIS compared to the absence of active stimulation.

Lastly, although broad network similarities can be seen in MDD, there is considerable person-to-person variance. Future therapeutic approaches should acknowledge and accommodate this fact, including sex-, age-, and head size-specific differences in treatment response. As the tTIS technology develops further, we envisage a more ambitious, effective, personalized therapy design based on individual-level modeling with personalized neuroimaging. Our group-level optimization represents one modest step in this direction, and we hope to perform individual-level tTIS modeling *post hoc* using the acquired MRI scans. If our clinical trial shows successful engagement of the sgACC with tTIS using resting-state MRI, this will warrant further investigation of tTIS effects in MDD using task-based neuroimaging, individual-level modeling, and manipulation of the tTIS parameters space. We aim to encourage the transition in clinical psychiatry away from the trial-and-error, black-box regime of 20th-century medicine and toward personalized medicine, underwritten by computational modeling and precision engineering.
